### Secondary aim

The secondary outcome of the study will be the efficacy of n-3 PUFA to prevent relapse in first-episode schizophrenia. Hence, the secondary null hypothesis will be that intervention is not different from placebo on the efficacy measure. Using the relapse rate as the secondary endpoint a one-sided log-rank test with an overall sample size of 82 subjects (41 per study arm) will achieve a 90.2 % power at a 0.05 significance level to detect a difference of 20 percentage points (regarded as clinically significant) in the relapse rate. Intention-to-Treat basis (ITT) will be used in analyses. Analysis of secondary endpoint will be by the Last Observation Carried Forward (LOCF) principle. The secondary outcome measure will be interpreted at 0.05 significance level.

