#### n-3 PUFA in relapse prevention

To date, only one study of the use of n-3 PUFA in relapse prevention has been reported. Emsley et al. recently published the results of a study assessing the efficacy of intervention composed of 1 g of DHA and 2 g of EPA plus 300 mg of the antioxidant alpha-liopic acid (LA) or placebo in patients diagnosed with schizophrenia, schizoaffective disorder or schizophreniform disorder meeting the criteria of relapse in whom antipsychotic therapy was tapered and discontinued according to the current guidelines. The study was terminated prematurely due to the severity of some of the relapse episodes, as well as the high relapse rates in both treatment groups: 90% and 75% in active and placebo groups respectively. The authors did not observe significant differences in relapse rates between the study arms. The study concludes that n-3 PUFAs + alpha-LA does not appear to be a suitable alternative to maintenance antipsychotic treatment in relapse prevention. The authors argue that on the basis of their findings, the current treatment guidelines suggesting antipsychotic discontinuation 2–3 years after the first psychotic episode should be revised [43].

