The analysis of covariance (ANCOVA) with intervention type as term and baseline PANSS score as covariate will be used to assess the change from baseline in PANSS scores to week 8 and 26 separately. If the overall ANCOVA of the baseline-to-endpoint change score will be significant, pairwise comparison will be performed using Dunnett t test. Analyzes will be two-sided for both ANCOVA and Dunnett test with the type I error rate for rejecting null hypothesis set at 0.05. The same analyses will be repeated to assess the significance of differences in changes of CDSS, CGI and GAF scores between the study arms.

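### The relapse test is one-sided at 0.05 with no stated reason, although its null is non-directional and the plan's symptom and functioning analyses are two-sided at 0.05

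*Protocol article*

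**What the plan says.** All of this is in the protocol article.

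- **Relapse, null hypothesis** (Secondary aim): "the secondary null hypothesis will be that intervention is not different from placebo on the efficacy measure". No direction is given.
- **Relapse, test** (Secondary aim): "a one-sided log-rank test with an overall sample size of 82 subjects (41 per study arm". No other test for relapse is named, and no reason for one-sidedness is given.
- **Relapse, power** (Secondary aim): the stated power is 90.2% at the 0.05 level, for an absolute difference in relapse of 20 percentage points. Neither the control relapse rate nor a hazard ratio is stated.
- **Relapse, interpretation** (Secondary aim): "The secondary outcome measure will be interpreted at 0.05 significance level". The level is not halved to allow for the one-sided test.
- **PANSS** (Primary aim): "Analyzes will be two-sided for both ANCOVA and Dunnett test with the type I error rate for rejecting null hypothesis set at 0.05". The article then applies this approach to CDSS, CGI and GAF as well.
- **Primary power** (Power calculation): two-sided at 0.05.
- **Earlier evidence on relapse** (n-3 PUFA in relapse prevention): the article knows of one earlier n-3 relapse-prevention study, with relapse rates of "90% and 75% in active and placebo groups respectively". The difference was not significant, and the study withdrew antipsychotics.

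**The concern.** A null of no difference, with no direction attached, has as its natural alternative a difference either way. A one-sided test does not match it unless the adverse direction is argued to be impossible or of no interest, and the article makes no such argument.

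Having a directional aim does not explain the exception. The primary aim, reducing symptom severity, is just as directional and is tested two-sided. Relapse alone is held to the weaker standard.

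Two things are at stake. A benefit on relapse could be claimed at a critical value of 1.645, where the other named clinical outcomes need 1.96. And if relapse were more frequent on active, the planned test would return only a non-significant result, whatever the size of the excess.

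**Working it through.** **1. Error rate in the direction of benefit.** One-sided 0.05 rejects when z is beyond 1.645 in favour of active, the same cut-off as two-sided 0.10. Two-sided 0.05 puts 0.05/2 = 0.025 in that direction. So the chance of a false claim of benefit is 5% as planned, against 2.5% under the standard used for PANSS, CDSS, CGI and GAF.

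**2. The stated 90.2%.** It cannot be uniquely reproduced, because no control rate is given. The check used 41 per arm, control rate pc, active rate pt = pc − 0.20, hazard ratio HR = ln(1 − pt)/ln(1 − pc), and events = 41 × (pc + pt). One-sided at 0.05, 90.2% is reached only at these rates:

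- Schoenfeld: about 25.5% v 5.5%, or 93.1% v 73.1%.
- Freedman: about 94% v 74%.
- Two proportions: about 21% v 1%, or 99% v 79%.

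Two-sided Schoenfeld also reaches it, at about 24% v 4%. The figure alone therefore does not establish sidedness; the wording does.

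**3. Cost of two-sided testing on the plan's own terms.** Take 90.2% at face value.

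- Implied standardised effect: z(0.95) + z(0.902) = 1.645 + 1.293 = 2.938.
- Power at two-sided 0.05 or one-sided 0.025: Φ(2.938 − 1.960) = Φ(0.978) = 83.6%.
- Patients needed to keep 90.2%: 82 × [(1.960 + 1.293)/2.938]² = 100.5, so about 101, or 102 for equal arms.

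**4. Cost at an assumed control rate.** The section Relapse in schizophrenia gives about one third relapsing before one year after recovery. Using it as the control rate is an assumption, because this trial counts from the acute phase.

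- HR = ln(0.8667)/ln(0.6667) = 0.353; events = 41 × 0.4667 = 19.1.
- Schoenfeld: √(19.13/4) × |ln 0.353| = 2.278. One-sided Φ(2.278 − 1.645) = 73.7%; two-sided Φ(2.278 − 1.960) = 62.5%.
- Freedman: √19.13 × (1 − 0.353)/(1 + 0.353) = 2.092. One-sided Φ(0.447) = 67.3%; two-sided Φ(0.132) = 55.3%.

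The range over other control rates, each with a 20-point difference:

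| Control v active | Schoenfeld, one-sided → two-sided | Freedman, one-sided → two-sided |
|---|---|---|
| 25% v 5% | 91.6% → 85.6% | 78.8% → 68.6% |
| 33.3% v 13.3% | 73.7% → 62.5% | 67.3% → 55.3% |
| 50% v 30% | 60.2% → 47.7% | 57.6% → 45.1% |
| 90% v 70% | 83.7% → 74.7% | 81.4% → 71.8% |

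In this table the change of sidedness costs about 6 to 13 percentage points. The rest of the distance from 90.2% comes from the control rate.

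**5. The adverse direction.** A log-rank simulation (4,000 runs, exponential times, 41 per arm) used 75% relapse on placebo and 90% on active. The one-sided test for benefit rejected in 0% of runs. A two-sided 0.05 test flagged the excess on active in about 55%.

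**The case against.** **Is the final test fixed as one-sided?** The term appears once, within the power sentence, and the sentence on interpretation gives only a level. It could be read as a one-sided power statement whose final test is left open. But no other relapse test is named, so one-sided is the natural reading. On the other reading, the stated power belongs to a test that will not be used. The section needs correcting either way.

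**Is this only a secondary endpoint, openly prespecified?** Yes. A reader can double the p-value, and the primary conclusion is untouched. That limits the weight of the point but does not remove the inconsistency.

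Four stronger readings are tempting, and the documents do not support them:

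- *The type I error is inflated beyond what is declared.* It is not. A one-sided test at 0.05 has an error of 0.05, as stated. Only the error in the direction of benefit doubles, and only relative to the two-sided standard used elsewhere.
- *The trial cannot detect harm.* Only the formal relapse test cannot. Relapse is assessed at every visit after the first, adverse events are recorded at all assessment visits, and PANSS, CDSS, CGI and GAF are compared two-sided.
- *Earlier evidence shows harm.* The 90% v 75% trial was not significant, stopped early, withdrew antipsychotics and added alpha-lipoic acid, whereas here n-3 is added to antipsychotic treatment. The symptom worsening with EPA described under Rationale for intervention arms was in chronic patients in exacerbation with low red-cell PUFA. Neither shows harm in first-episode patients; they only leave no basis for ruling it out.
- *Two-sided testing would cut power from 90.2% to 55–63%.* Most of that fall comes from the assumed control rate, which is a separate matter.

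**Conclusion.** The point holds as an internal inconsistency. The Secondary aim section pairs a non-directional null with an unexplained one-sided test at 0.05, while the primary power calculation and the PANSS, CDSS, CGI and GAF analyses are two-sided at 0.05. The article does not state sidedness for the cognitive, imaging, biochemical or metabolic measures, so the comparison goes no further than that.

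The consequence is a 5% instead of 2.5% chance of a false claim of benefit on relapse, and a formal relapse test that cannot declare an excess on active. The error-rate comparison rests on no assumption beyond the plan's own two-sided standard.

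The power cost does rest on assumptions: 90.2% to about 84% if the stated power is accepted, or about 67–74% to 55–63% if 33.3% v 13.3% is assumed. This should be corrected, but it does not threaten the primary analysis.

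**What to change.** In the Secondary aim section, specify a two-sided log-rank test at 0.05 for relapse, or equivalently for a claim of benefit a one-sided test at 0.025. The two-sided form is preferable because it matches the stated null and lets an excess on active be declared. Restate the power on that basis, with the control and active relapse rates it assumes. Make the change before the randomisation key is released, since a later change of sidedness would look data-driven.

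The cost is wording and a less favourable stated power: about 84% with 82 patients on the plan's implied effect. Holding 90.2% would need about 102 patients, but enlarging the trial for a secondary endpoint is not required by this point.

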### Relapse in schizophrenia

#### Relapse in schizophrenia

It is estimated that up to 90% of individuals developing first-episode schizophrenia achieve remission from symptoms in the first 12 months of therapy [34] but recovery defined as attainment of both functional and symptomatic remission for 2 years [35] is achieved in only 10-20% of patients [36]. This is partly because a great number of patients will experience a relapse of psychotic episodes during the first years following diagnosis. Longitudinal studies find that about one third of patients will have experienced a relapse before 1 year after recovery, and two thirds before 2 years [37,38]. Seventy to eighty percent of patients experience relapse within three to five years [39]. There is some evidence that with recurring episodes of psychosis, the time to obtain response increases and the proportion of patients achieving remission diminishes [40]. Psychotic relapse and incomplete recovery can lead to the chronic phase of the disease. Neurodegeneration and deterioration occurs mainly in the first 5–10 years of illness. The long-term outcome of the disease may be associated with the number of relapses and the quality of remission achieved [40]. These observations have generated increased interest in relapse prevention in schizophrenia and have prompted repeated attempts to understand the risk factors responsible for recurrence of the psychotic exacerbation.

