### Power calculation

Previous studies have suggested medium effect sizes in favor of n-3 fatty acids [21,22]. On the basis of previous studies, we assume that there will be a nontrivial correlation between baseline and outcome scores at follow-up, and it is hypothesized that baseline scores will explain 25% of the variation in outcome measures. Power calculation revealed that 36 participants per study arm will result in 80% power to detect medium effect size (0.3) at a significance level of 0.05 (two sided). Assuming an attrition rate of 15%, we aim to enroll 82 patients.

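### The 90.2% power for relapse rests on an undeclared placebo rate and no dropout; at the document's only one-year relapse figure it is about 61–74%

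*Protocol article*

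**What the plan says.** In the Secondary aim section of the statistical methods, the relapse comparison is powered as "a one-sided log-rank test with an overall sample size of 82 subjects (41 per study arm"). This design "will achieve a 90.2 % power at a 0.05 significance level" and is meant "to detect a difference of 20 percentage points (regarded as clinically significant) in the relapse rate". No placebo rate, active rate, hazard ratio, expected number of events or dropout is given. The analysis is by intention to treat with last observation carried forward.

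Two other places bear on this figure:

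- The Power calculation section, for the PANSS outcome, says that "36 participants per study arm will result in 80% power" and then: "Assuming an attrition rate of 15%, we aim to enroll 82 patients". So 82 is an enrolment target that already includes expected losses.
- The Background section on relapse in schizophrenia reports that "about one third of patients will have experienced a relapse before 1 year after recovery, and two thirds before 2 years". This is the only one-year relapse figure in the document.

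**The concern.** The power of a log-rank test depends on the number of events and the hazard ratio. A fixed 20-point gap gives different values of both at different placebo rates, so a power quoted to one decimal place cannot be checked, or relied on, without that rate. When the document's only one-year figure is used, the result is well below 90.2%.

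The relapse calculation also treats all 82 enrolled patients as fully observed, while the calculation that produced 82 expects 15% to be lost. Relapse is followed to week 52, longer than the week-26 primary outcome, so losses should be no smaller.

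Relapse prevention is the first secondary aim, one of the research questions and part of the abstract. A reader who takes 90.2% at face value would give a null relapse result more weight than the design supports.

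**Working it through.** **Inputs.** From the Secondary aim section: 41 per arm, one-sided 0.05 (z = 1.645), a 20-point difference and stated power 90.2%. From the Power calculation section: 15% attrition, and 41 × 0.85 = 34.85, about 35 per arm. From the Background: a one-year relapse rate of about one third, used here as a stand-in because no design rate is declared.

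**Formulas.** With placebo rate p1, active rate p2 = p1 − 0.20 and n per arm:

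- HR = ln(1 − p2) / ln(1 − p1)
- events d = n(p1 + p2)
- Schoenfeld: power = Φ(½·√d·|ln HR| − 1.645)
- Freedman: power = Φ(√d·(1 − HR)/(1 + HR) − 1.645)

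**Step 1: what gives 90.2%?** The placebo rate was solved for at n = 41.

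- Schoenfeld gives 90.2% at p1 = 25.5%: HR = ln(0.945)/ln(0.745) = 0.192, d = 41 × 0.31 = 12.7, z = ½ × 3.565 × 1.649 = 2.94, and Φ(2.94 − 1.645) = 0.902. It gives 90.2% again at p1 of about 93%.
- Between those two rates it is lower: 79.5% at p1 = 30%, 66% at 40%, 60% at 50%, with a minimum of 59% near 58%.
- Freedman reaches 90.2% only at about 94%. At the low end it stays below 89%.

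The stated figure is therefore attainable by one standard formula, at roughly 25% v 5%. That is an 80% relative reduction (20/25) resting on about 12 events.

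**Step 2: the document's one third, no loss.** 33.3% v 13.3%, n = 41:

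- HR = ln(0.867)/ln(0.667) = 0.353; d = 41 × 0.467 = 19.1
- Schoenfeld: z = ½ × 4.374 × 1.042 = 2.278, power Φ(0.633) = 73.7%
- Freedman: z = 4.374 × 0.647/1.353 = 2.092, power Φ(0.447) = 67.3%

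At these rates 90.2% would need about 32 events (Schoenfeld) to 38 (Freedman), or about 69 to 81 patients per arm.

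**Step 3: the same rates with 15% lost.** n = 35, d = 35 × 0.467 = 16.3:

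- Schoenfeld: z = ½ × 4.041 × 1.042 = 2.105, power 67.7%
- Freedman: z = 4.041 × 0.478 = 1.933, power 61.3%

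**One-sided results, with a simulated log-rank test (exponential times) as a check**

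| Setting | Schoenfeld | Freedman | Simulated |
|---|---|---|---|
| 25% v 5%, 41 per arm | 91.6% | 78.8% | 86% |
| 33.3% v 13.3%, 41 per arm | 73.7% | 67.3% | 71% |
| 33.3% v 13.3%, 35 per arm | 67.7% | 61.3% | 65% |
| 33.3% v 13.3%, 41 per arm, 15% censored over the year | – | – | 67–68% |

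**Sensitivity case only.** A two-sided 0.05 test, which the plan does not specify for relapse, gives 62.5% (Schoenfeld) and 55.3% (Freedman) with 41 per arm, and 55.7% and 48.9% with 35.

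**The case against.** The best defence has four parts.

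- **One third is not the design rate.** It comes from the background literature and is timed from recovery. The trial counts from enrolment in the acute phase and uses a five-part composite definition of relapse. This stands: one third is a proxy, and the Secondary aim section does not contradict the Background. The proxy need not be exact for the point to hold, though. By Schoenfeld, with no loss, power is below 80% at any placebo rate from 30% to about 87%.
- **The figure can be reproduced.** At about 25% v 5% Schoenfeld gives 90.2% or a little more. This also stands. A reader might infer a proven arithmetic error, and the document does not support that. What it shows is an undeclared input and a figure that holds only in a narrow low range or at very high relapse rates. Even at 25% v 5% the simulated test gives about 86%.
- **An article may leave detail to the full protocol.** This is true of a missing assumption on its own. Here the article publishes the resulting power to one decimal place, and that power is not reached at the only one-year rate it reports.
- **Attrition matters less than it looks.** Intention to treat with carried-forward observations keeps dropouts in the analysis, so deleting 15% of patients is the harshest approximation. This stands: treated as censoring, the loss costs about 3 to 4 points. Most of the shortfall comes from the placebo rate.

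A reader might also infer that power is nearer one half. That follows at a one-third placebo rate only if a two-sided test is substituted. Whether a one-sided test is appropriate is a separate question and should not be used to lower this figure.

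**Conclusion.** The point holds in a limited form. The 90.2% cannot be rebuilt from what is stated, because the placebo rate that determines it is missing, and it takes no account of the attrition the same document expects. If placebo relapse is about one third, the planned one-sided test has about 67–74% power with complete follow-up and about 61–68% with 15% of patients removed (about 67% under censoring). The chance of detecting a 20-point difference is then roughly two in three, not nine in ten.

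These figures assume proportional hazards with exponential times, equal arms, and one third as a stand-in for the trial's own composite relapse rate.

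Severity is moderate. Relapse is a secondary endpoint, the 82 comes from the PANSS calculation, and no estimate, test or trial procedure depends on the 90.2%.

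**What to change.** In the Secondary aim section, state the assumed one-year placebo relapse rate and dropout, name the method, and replace 90.2% with the power these give. One possible wording: *with 41 patients per arm and a one-sided 0.05 log-rank test, power to detect a 20-point reduction is about 61–74% if one-year relapse on placebo is one third, depending on method and dropout.* Alternatively, keep 90.2% and justify a placebo rate that supports it for this trial's relapse definition and time origin, with dropout included.

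Report the difference in relapse with a confidence interval, so that a null result is read by its precision and not by a nominal power. If two-sided power is also shown (about 49–63% at one third), label it as a sensitivity case.

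The cost is wording and a less favourable published power. The sample size, the test and the conduct of the trial need not change.

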### Statistical methods and analytic plan

#### Primary aim

The primary aim is to assess the efficacy of add-on n-3 PUFA therapy in reducing the severity of symptoms in schizophrenia patients after 26 weeks supplementation accompanying standard antipsychotic treatment. Hence, our primary outcome measure is the change observed over time on the total and subscale PANSS scores. The changes in the scores will be calculated by subtracting baseline from follow-up score at each follow-up assessment visit for each patient. Efficacy analyses will be performed using the modified intent-to-treat (ITT) population, which will consist of all randomized patients who will receive at least one daily dose of either placebo or active compound and have at least one efficacy evaluation on day seven or later. Observed case analysis will also be performed for the primary and secondary outcome measures.

Comparisons between treatment groups at baseline will be conducted using a one-way analysis of covariance, with intervention type as a term in the model and duration of untreated psychosis (DUP) as covariate. The distribution of socio-demographic characteristics in the two treatment arms will also be compared to assess the effectiveness of the randomization procedure.

To deal with missing values in our ITT sample, a multiple imputation technique will be used, in which a number of data sets are created, each with the missing values replaced by some plausible values. The imputation of the missing values is based on maximum likelihood and Bayesian procedures and is performed by appropriate algorithms. After the missing cases are completed by several sets of plausible values to create multiple completed datasets, standard complete-data procedures are applied to each completed dataset, and finally the multiple sets of results are combined to yield a single inference. The multiple imputation technique is considered superior to and less biased than the Last Observation Carried Forward (LOCF) [53,77].

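### Relapse is to be analysed by LOCF alongside a log-rank test; on the usual reading this biases one-year relapse rates down and, if dropout differs by arm, shifts the one-sided error rate up or down depending on which arm loses more

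*Protocol article*

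**What the plan says.** All references are to the Protocol article.

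- **Test.** The Secondary aim section names one test for relapse, in its power sentence: "Using the relapse rate as the secondary endpoint a one-sided log-rank test", with "an overall sample size of 82 subjects (41 per study arm"), powered "to detect a difference of 20 percentage points (regarded as clinically significant) in the relapse rate".
- **Analysis set and missing data.** The same paragraph states "Intention-to-Treat basis (ITT) will be used in analyses", and then "Analysis of secondary endpoint will be by the Last Observation Carried Forward (LOCF) principle". Censoring is not mentioned.
- **Level.** "The secondary outcome measure will be interpreted at 0.05 significance level".
- **The plan's own view of LOCF.** The Primary aim section handles missing values in the ITT sample by multiple imputation, because "The multiple imputation technique is considered superior to and less biased than the Last Observation Carried Forward (LOCF"). It also plans an observed case analysis for both primary and secondary outcomes.
- **Exposure.** The Power calculation section states "Assuming an attrition rate of 15%, we aim to enroll 82 patients". Attrition is not split by arm. Relapse is judged at every post-baseline visit (weeks 1, 2, 4, 6, 8, 16, 26 and 52), so the last interval between assessments is 26 weeks.

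**The concern.** A log-rank test deals with incomplete follow-up by taking a patient out of the risk set when observation ends. Carrying a relapse status forward does something else. A patient last seen relapse-free at week 8 would be treated as observed and relapse-free for the remaining 44 weeks. The numerator loses the relapses that went unseen, while the denominator keeps the patient.

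Two things are at stake. The one-year relapse rates, the figures readers will take from this endpoint, come out too low. And if the arms lose different numbers of patients, the arm that loses more looks better for that reason alone. The plan also applies to its first secondary aim, without giving a reason, the method it has just set aside for the primary outcome as more biased.

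**Working it through.** **Inputs from the article.** 41 per arm; one-sided log-rank test at 0.05; 20-point difference; 15% attrition; 52 weeks with the visit weeks above.

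**Assumed, because not stated.** The control relapse rate is taken as 33%, since the Background (Relapse in schizophrenia) cites about one third within a year of recovery; 50% is used as a second value. Dropout by arm is varied from 0% to 30%. Relapse and dropout times are exponential and independent of each other, so dropout is non-informative.

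**Step 1. The plan's own figure.** The stated power of 90.2% cannot be reproduced, because no control rate is given. Take events D = 41 × (pC + pT), HR = ln(1 − pT)/ln(1 − pC) and power = Φ(½√D × |ln HR| − 1.645). At 33% v 13% this gives D = 18.9, HR = 0.348 and power 74%. Values near 90.2% appear only around 25% v 5% (91.6%), 26% v 6% (88.9%) or 93% v 73% (89.9%). That is a separate matter and does not bear on LOCF.

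**Step 2. Reported one-year rate under LOCF.** Let p be the true relapse rate, d the dropout rate, L = −ln(1 − p) and M = −ln(1 − d). Only relapses that precede dropout are seen, so the reported rate is L/(L + M) × [1 − (1 − p)(1 − d)].

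- p = 33%, d = 15%: 0.4005/0.5630 × (1 − 0.67 × 0.85) = 0.7113 × 0.4305 = 30.6%.
- p = 13%, d = 15%: 0.1393/0.3018 × (1 − 0.87 × 0.85) = 0.4615 × 0.2605 = 12.0%.
- The 20-point difference becomes 18.6 points. Simulations on the trial's visit weeks gave 30.4% v 12.0% and 29.9% v 11.7%, so about 18 points.
- p = 50%, d = 15%: 46.6%.
- If all dropouts leave at week 8, 33% is reported as 0.85 × 0.33 + 0.15 × (1 − 0.67^(8/52)) = 0.2805 + 0.0090 = 28.9%.

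Kaplan-Meier with censoring at dropout recovered 33% and 50% in simulation.

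**Step 3. Equal dropout of 15%.** With no true effect (33% in both arms), one-sided rejection is 4.9% with LOCF and 5.2% with censoring. At 33% v 13%, power is 66.3% with LOCF and 67.2% with censoring. The test is essentially unaffected.

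**Step 4. Unequal dropout.** At 10% placebo and 25% active, with a true 33% in both arms, the Step 2 formula gives:

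- placebo: 0.4005/0.5058 × (1 − 0.67 × 0.90) = 31.4%;
- active: 0.4005/0.6882 × (1 − 0.67 × 0.75) = 29.0%.

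That is a spurious gap of about 2.5 points in favour of active. One-sided rejection with no true effect, from 3,000 to 5,000 simulated trials per scenario (Monte Carlo standard error about 0.3 to 0.7 points; ranges are the results of separate runs):

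| Relapse, both arms | Dropout placebo/active | LOCF | Censoring |
|---|---|---|---|
| 33% | 12.5/17.5% | 5.5-6.3% | not tabulated |
| 33% | 10/20% | 6.9-7.1% | 4.7-5.1% |
| 33% | 10/25% | 8.6-9.5% | 5.1-5.2% |
| 33% | 5/25% | 9.1% | 4.9% |
| 33% | 0/30% | 11.4% | 4.6% |
| 33% | 25/10% | 2.6% | not tabulated |
| 33% | 25/5% | 2.4% | 5.0% |
| 50% | 5/25% | 10.9% | 4.9% |
| 50% | 0/30% | 14.9% | 5.1% |

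When placebo loses more, the cost is power: at 33% v 13% with 25/5% dropout, 57.8% with LOCF against 67.4% with censoring.

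**The case against.** **Mechanics.** The article never says that dropouts are followed artificially to week 52. A log-rank test censors by construction, so the two sentences could be called merely unreconciled. This stands as a caveat: the effects above are conditional on the usual reading of LOCF for a relapse status. But the article offers no other reading, and the LOCF rule is stated, not left open.

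**Direction.** A reader might infer that any imbalance in dropout inflates the false-positive rate. For the planned one-sided test it does not: inflation needs more loss on active, and more loss on placebo makes the test conservative. A reader might also infer that the supplement will cause more dropout. Nothing in the article supports that. It describes the supplement as safe and well tolerated and makes the capsules comparable in taste. The larger figures in the table therefore illustrate a possibility; they are not a forecast. With equal 15% attrition, only the rates move.

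**Existing safeguard.** LOCF is not the only analysis, since an observed case analysis is planned for secondary outcomes too. It is a partial check: it is additional, it does not define censoring, and LOCF remains the stated main rule.

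**Limits of censoring.** Patients who leave may be those who are worsening or stopping antipsychotics; the article itself names discontinuation as the main relapse risk factor. In that case censoring and Kaplan-Meier are biased as well. This stands in full, and is why the fix cannot stop at censoring. The calculations assume non-informative dropout, and the informative case was not computed.

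**Conclusion.** The point holds in limited form. LOCF does not fit the log-rank test named for relapse, and the article itself rates it as more biased than multiple imputation.

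The downward bias in the one-year rates needs only dropout and the usual reading of LOCF: about 2 to 3 points at a true 33% with 15% attrition spread over the year, and about 4 points if all dropouts leave at week 8. The effect on the test depends on a dropout split that the article does not give. It is negligible if dropout is equal, anti-conservative if the active arm loses more, and conservative with lost power if placebo loses more. All sizes rest on the assumed relapse rates, exponential times and non-informative dropout.

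This should be fixed, but it is not fatal to the trial. It concerns a secondary endpoint, and the primary PANSS analysis uses multiple imputation and is untouched.

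**What to change.** Delete LOCF for relapse. Replace it with wording such as: patients without relapse are censored at their last completed relapse assessment; the arms are compared by the log-rank test; one-year relapse is estimated by Kaplan-Meier in each arm.

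State that censoring assumes dropout is unrelated to relapse risk. Add a sensitivity analysis for informative dropout, for example counting dropouts as relapsed, labelled as an extreme bound. Report dropout by arm, so that readers can see which of the cases above applies.

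The cost is a few sentences of analysis wording and one extra analysis. No new data or visits are needed. The change should be made before unblinding, so that it cannot be taken as driven by the results.
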